**1.** Evaluate recent BP, HR, UO, sCr, HCT, Net intake/output **2.** Consider decreasing UF rate by 50 cc/hr. and checking STAT sCr (unless sent in past 2 h) if: **a.** sCr rise > 15% or > 0.2 mg/dl (whichever is less) compared to prior measurement **b.** HCT rises by > 5% compared to prior measurement **c.** resting SBP decreases > 10 mmHg compared to prior 6 h, but remains > 80 mmHg **d.** UO drops > 50% compared to prior 6 h, but remains > 125 cc/6 h **e.** resting HR increases by > 20 bpm compared to prior 6 h, but remains < 120 bpm **3.** Strongly consider holding UF and checking STAT sCr if: **a.** sCr rise by > 30% or > 0.4 mg/dl (whichever is less) compared to prior measurement **b.** HCT rises by > 10% compared to prior measurement **c.** resting SBP decreases > 20 mmHg compared to prior 6 h or is < 80 mmHg **d.** UO < 125 cc/6 h **e.** resting HR increases by 30 bpm compared to prior 6 h or is > 120 bpm **4.** If UF held, re-evaluate after laboratory values are available: **a.** If hemodynamics is stable and sCr has plateaued, then consider re-starting UF at rate 50-100 cc/hr. less than previous rate **b.** If persistent volume overload is present, then consider: **i.** Adjusting doses of IV inotropes in patients with LVEF < 40% or RV systolic dysfunction **ii.** Weaning venodilators, especially in patients with HFpEF **iii.** Right heart catheterization	
D. Consider completion of UF therapy If ONE of the following occurs:	
**1.** Resolution of congestion (all of following): **a.** Jugular venous pressure < 8 cm H_2_O **b.** No orthopnea **c.** Trace or no peripheral edema **2.** Best Achievable “Dry Weight” has been reached **a.** Evidence of poor tolerance of fluid removal AND **b.** UF rate < 100 cc/hr. or net negative < 1 l/24 h **3.** Persistent elevation in sCr > 1.0 mg/dl above baseline at start of UF treatment **4.** Persistent hemodynamic instability	
E. After completion of UF Therapy:	

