### Study outcomes

The primary end points of EUC-CHF are the changes of weight loss and dyspnea severity score at every scheduled visit which are considered as the part of a single composite endpoint, as well as the occurrence of clinically major bleeding defined by TIMI or GUSTO criteria [12].

Secondary outcomes include: net fluid loss, length of stay in CCU or ICU, change of score by MLWHFQ functional capacity, change of serum and ultrafiltrate concentrations of endotoxin, ET-1, TNF-a, IL-6 and IL-10, changes of cardiac function (the NYHA classification), changes in N-terminal proB-type natriuretic peptide (NT-proBNP) level, changes of LDs dose, HF rehospitalizations for congestive HF in 30 days after discharge, cardiovascular death and all-cause death in 30 days after discharge, change of blood pressure, changes in hepatic and renal function (serum creatinine concentration, estimated glomerular filtration rate [eGFR]), serum electrolytes, hemoglobin and incidence of acute coronary syndrome at scheduled visits.

Weights will be obtained at every scheduled visit using the same balance with the patient shoeless in a hospital gown after emptying the bladder. Weight loss is the difference between weight at baseline and the weight recorded at subsequent visits.

The dyspnea severity score by a proposal to standardize dyspnea measurement in clinical trials of acute heart failure syndromes by International Working Group on acute heart failure of European Society of Cardiology is used for the assessment of dyspnea [13].

Total fluid intake and output (ultrafiltrate and urine) measured at every scheduled visit after enrollment will be used to calculate net fluid losses.

Glomerular filtration rate will be calculated according to the abbreviated Modification of Diet in Renal Disease (MDRD) equation [14].

Acute coronary syndrome includes unstable angina, ST segment elevated myocardial infarction and non-ST segment elevated myocardial infarction. Myocardial infarction is defined according to the fourth universal definition of myocardial infarction [15]. Death will be considered cardiac according to the 2014 ACC/AHA key data elements and definitions for cardiovascular endpoint events in clinical trials [16].

We also will collect all the urine output after patients are enrolled to receive standard medical therapy or early UF until 72 h after the end of study treatment. Then we will measure the average urine electrolytes for every enrolled patient.

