Although theoretically UF specific filter membrane could only penetrate small molecules such as sodium and water, there is no previous evidence from clinical studies on whether UF could filter out inflammatory mediators. It is not exactly certain whether UF is able to remove inflammatory mediators. Previous research found that high-volume continuous veno-venous hemofiltration combined with periodic filter change, different UF rates, different membrane pore sizes, different types of membrane, and different species were all related to the efficacy of removing inflammatory mediators by hemofiltration [34–36]. The capacity of filtering out mediators by UF specific filter membrane is influenced by many factors, such as pore size, screening coefficient of the membrane, molecular charge and molecular weight of the mediators. It is difficult to determine whether they can be filtered out only by the molecular weight of the mediators alone. Therefore, we will measure changes of serum and ultrafiltrate concentrations of inflammatory mediators including endotoxin, endothelin-1 (ET-1), tumor necrosis factor- (TNF-a), interleukin-6 (IL-6) and IL-10 in our study. We try to find out whether UF could relieve both fluid overload and other clinical manifestations such as HF related multiple organ dysfunction syndrome (MODS) in acute HF by filtering out certain inflammation mediators. Our study will provide further data regarding the ability of UF to filter out inflammation mediators. To our knowledge, this is the first trial exploring the effects of UF on circulating inflammatory mediators.

The present study is mainly limited by its open-label design and patient selection bias cannot be excluded, which will make the interpretation of the results somewhat limited. Also, the follow-up period is relatively short in our trial. Postpone the last clinical evaluation at 90 days and at an even later time point may provide more information of the advantages or disadvantages of UF.

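### The mediator outcome is a change in raw concentration, which does not measure how much UF removes and lets lost plasma water mask removal in serum

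*Protocol article*

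**What the plan says.** Under Study outcomes, the secondary outcomes include "change of serum and ultrafiltrate concentrations of endotoxin, ET-1, TNF-a, IL-6 and IL-10". The Discussion repeats the definition: "we will measure changes of serum and ultrafiltrate concentrations of inflammatory mediators". Neither place mentions an amount removed, an ultrafiltrate-to-serum ratio, or an allowance for changing plasma volume.

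The Discussion asks several things of this outcome:
- whether removal is possible at all: "It is not exactly certain whether UF is able to remove inflammatory mediators";
- whether UF relieves clinical manifestations "in acute HF by filtering out certain inflammation mediators";
- what happens to blood levels: "this is the first trial exploring the effects of UF on circulating inflammatory mediators".

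It also promises that "Our study will provide further data regarding the ability of UF to filter out inflammation mediators".

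Data that would support a better measure are planned, but for other purposes. Under Study outcomes: "Total fluid intake and output (ultrafiltrate and urine) measured at every scheduled visit after enrollment will be used to calculate net fluid losses". Haemoglobin is a secondary outcome at the scheduled visits. Haematocrit is followed during UF to protect the kidney (Study overview). Table 2, section C, names among the findings that should prompt strong consideration of holding UF: "HCT rises by > 10% compared to prior measurement".

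**The concern.** A concentration is an amount divided by a volume, and UF acts on both. The ultrafiltrate concentration, taken alone, ignores how much fluid was drawn off. The serum concentration depends on how much plasma water is left as well as on how much mediator is left.

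The visits in the Study overview are baseline, end of treatment, three time points over the next 72 h, discharge and 30 days after discharge. Ultrafiltrate does not exist at the first of these or after treatment ends, and controls never produce any. A change over scheduled visits, or a difference between arms, therefore has no content for ultrafiltrate.

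What is at stake is how the mediator result is read. A flat or rising serum level could be taken to mean that UF does not clear mediators when part of it is lost water. A similar ultrafiltrate concentration in two patients could be taken as similar removal when the volumes differ widely.

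**Working it through.** The article states no figure for this outcome, so there is none to reproduce. The checks below are illustrations, with assumptions marked.

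**1. Ultrafiltrate: concentration against mass**

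Inputs: starting rates of 150, 200 and 250 cc/hr (Table 2, section A). Assumed: 24 h at a constant rate and 10 pg/mL (that is, 10 ng/L) in every patient.

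Mass removed = concentration × rate × time.
- 150 cc/hr: 3.6 L × 10 ng/L = 36 ng
- 200 cc/hr: 4.8 L × 10 ng/L = 48 ng
- 250 cc/hr: 6.0 L × 10 ng/L = 60 ng

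The ratio is 60/36 = 1.67 with an identical concentration result, and it depends on neither the 10 pg/mL nor the 24 h. Section B allows a 50 cc/hr reduction; a patient run at 100 cc/hr has 24 ng removed, and 60/24 = 2.5. Duration is not fixed (Study overview: one or more sessions until symptoms are relieved), so the real spread can be wider.

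**2. Serum: effect of lost plasma water on a retained solute**

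Inputs: haematocrit rises of 5% and 10% (the action triggers in Table 2, section C). Assumed: constant red-cell volume and baseline haematocrit H0 of 30% to 45%. The upper end matches the exclusion above 45%; the lower end is an assumption.

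Plasma-volume ratio R = [H0(1 − H1)] / [H1(1 − H0)]; a fully retained solute is multiplied by 1/R.
- 30% to 33%: R = (0.30 × 0.67)/(0.33 × 0.70) = 0.870, a rise of 14.9%
- 36% to 39.6%: R = (0.36 × 0.604)/(0.396 × 0.64) = 0.858, a rise of 16.6%
- 45% to 49.5%: R = (0.45 × 0.505)/(0.495 × 0.55) = 0.835, a rise of 19.8%

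A 5% relative rise gives 7.3% to 9.5%. Table 2 does not say whether its percentages are relative or absolute. Read as absolute points, 5 and 10 points give about 22% to 26% and 49% to 56%.

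**3. Serum: can removal be hidden?**

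Assumed: convective removal only, sieving coefficient S, no refill, production or other clearance, and plasma volume falling to f = 0.85 of its start. Mass left = f^S; C/C0 = f^(S − 1). The last column is C/C0 × f.

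| S | C/C0 (raw) | Mass removed | Corrected value |
|---|---|---|---|
| 0 | 1.176 | 0% | 1.00 |
| 0.5 | 1.085 | 7.8% | 0.922 |
| 1 | 1.000 | 15% | 0.85 |

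The raw value never falls, although up to 15% of the mass has gone. The corrected value recovers the mass left under these assumptions. It is not safe in general: if production rapidly restores a mediator to its set concentration, raw C/C0 is 1.00 and the corrected value is 0.85, although that 15% fall need not reflect filtration.

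**The case against.** Several points on the other side stand.

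- **The qualitative question is answered.** A reader might infer that the trial cannot show whether UF removes mediators. That goes too far: a measurable ultrafiltrate concentration shows passage through the membrane. Only the amount is undetermined by the stated outcome, and since volume is recorded, mass may be derivable from the planned data.
- **Table 2 is not a forecast.** It is tempting to read the 5% and 10% figures as expected haematocrit rises. They are triggers for slowing or holding UF, and the documents give no expected rise.
- **Between-arm bias is not shown.** A reader might infer a serum bias of 15% to 20% between arms. The control arm is also decongested, and the Study overview says its diuretic protocol takes haemoconcentration into account. Only the difference in plasma-volume change matters; Table 2 itself refers to plasma refill, and later visits may see little of it. If UF patients haemoconcentrate more, the effect masks removal rather than creating it.
- **Raw serum concentration is a legitimate measure** of circulating level, which is what the Discussion's novelty claim concerns. The corrected value should not displace it.
- **Haemoglobin should not be corrected the same way.** It is measured in whole blood. In the 36% to 39.6% example it rises by a factor of 1.10, and 1.10 × 0.858 = 0.944, a false fall of 5.6% with no blood lost. The method also assumes the constant red-cell volume that bleeding breaks, and major bleeding is a primary endpoint.

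It can also be said that this is one of many secondary outcomes, to be summarised descriptively, in a condensed article. Sampling and assay detail may well sit in a fuller document, and their absence is no fault. But the article does fix the measure itself, and for ultrafiltrate that measure cannot be read as an effect.

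**Conclusion.** The point holds in limited form. As defined, the ultrafiltrate change has no baseline and no comparator, and concentration alone leaves mass removed undetermined by a factor of 1.67 across the starting rates at equal duration, and by more as duration varies. That follows from Table 2 and the visit schedule by arithmetic.

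The raw serum change mixes removal with plasma-volume change. The 15% to 20% figure is conditional on a 10% relative haematocrit rise, constant red-cell volume and the assumed baseline range. It shows that masking is possible, not that it will occur to that extent. The size of any difference between arms cannot be stated from the documents.

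The primary endpoints are untouched. The gain is in whether the mediator results can support the statements about removal made in the Discussion.

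**What to change.** 1. In the UF arm only, replace the ultrafiltrate change with (a) mass removed = ultrafiltrate concentration × recorded ultrafiltrate volume, and (b) the ratio of ultrafiltrate to simultaneous serum concentration. The Discussion already names the membrane's screening coefficient as a determinant of filtering; (b) is its observed counterpart.
2. Keep the raw serum change as the between-arm comparison. Add in both arms, as a sensitivity analysis, the follow-up serum value multiplied by [H0(1 − H1)]/[H1(1 − H0)]. State that it assumes slow mediator turnover and stable red-cell volume.
3. Leave haemoglobin uncorrected.

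Cost: a little more analysis. Ultrafiltrate volume, both assays and haemoglobin are already planned. Two things need confirming: that ultrafiltrate is sampled from a pool or at recorded times, since a single spot sample does not give mass; and that haematocrit is recorded with the serum samples in both arms, since its monitoring is described only for the UF procedure in the text shown.

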Currently, UF recommend by most of the guidelines are usually considered for patients with refractory congestion not responding to medical therapy. Previous research found although UF improve hemodynamics in acute decompensated HF refractory to standard medical therapy, it was also associated with high incidence of renal function damage and high in-hospital mortality [6]. However, other research found UF within 12 h of hospitalization in HF patients with volume overload and LD resistance before IV LDs effectively decreased length of stay and readmissions up to 3 months without change of renal function [7]. At present, most of the studies support UF should be considered as early treatment strategies (24 h after admission) in patients with severe HF instead of a “rescue therapy”. Early UF may prevent undesirable cardiorenal syndrome and sodium-volume overload before renal tubular damage induced by further neurohormonal activation and side effects caused by high dose LDs [8, 9].

Taken together, previous related studies showed UF is more effective in decongestion, haemodynamic variables and clinical outcome improvement, as well as restoring LD responsiveness compared with LDs. But most of the studies were based on the foreign population and did not define the exact time period from admission to UF. We do not have the related data for early UF in Chinese population. Furthermore, former study did not define how to screen out the patients recommended for early UF by specific scoring system. Our study aims to determine if early UF 24 h within admission in acute HF is superior to IV LDs in clinical parameter improvement without adverse events and prevents rehospitalization up to 30 days in Chinese population.

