### Study overview

The EUC-CHF trial is an open-label, registry-based, prospective, single center study. It will recruit patients with severe acute decompensated HF who are hospitalized for HF worsening and significant weight gain due to overt fluid overload 24 h from hospital admission. The determination that acute decompensated HF is the primary cause of hospitalization will be made by the site’s principal investigator or sub-investigator, based on the assessment of the clinical signs and symptoms as well as laboratory examinations that lead to the admission. Patient enrollment should be completed and study treatment initiated within 24 h from hospital admission. Patients will be enrolled 1:1 sequentially to receive standard medical therapy (control group) or early UF (early UF group). Up to 2 doses of IV LDs will be allowed before enrollment.

The diuretic protocol adopted by our study in the control group refers to the protocol of AVOID-HF and CARRESS-HF trial as well as the dose recommended by the guideline according to patients’ vital signs, status of hemoconcentration, and renal function (Table 1) [10, 11]. Patients of the early UF group will be treated with a single or repeated session of UF within 24 h from admission (according to local clinical practice and with availability of nursing surveillance during UF) until the relief of patient’s symptom. The UF protocol adopted by our study also refer to the protocol of AVOID-HF and CARRESS-HF trial (Table 2).

[figure not shown]

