**Fig. 1 Fig1:**
[figure not shown]
Study design. The control group will be treated with intravenous loop diuretics by experienced HF cardiologists according to guideline recommendations. Patients of the early UF group will receive a single or repeated session of UF started within 24 h from admission until the relief of patient’s symptom. HF, heart failure; UF, ultrafiltration

The trial aims to recruit 40 patients (20 patients for each group) over an estimated 24-month period. After baseline visit, follow-up visit will occur at the end of study treatment, 24 h, 48 h, and 72 h after the end of study treatment, at discharge, and 30 days after discharge. At the baseline visit, informed consent will be taken, and additional baseline variables including gender, age, height, weight, occupation, race, physical activity, complete medical history (including history of smoking and drinking, past and present medical history, concomitant disease), vital signs, NYHA classification, dyspnea severity score, score by Minnesota Living with Heart Failure Questionnaire (MLWHFQ) functional capacity, physical examination including distention of jugular vein, edema of lower extremity and congestion of other organs, laboratory test, electrocardiogram, chest X-ray, echocardiographic data and concomitant drug used up to 3 months before enrollment will be recorded.

Questionnaires (dyspnea severity score and score by MLWHFQ functional capacity) at follow-up visits will also be collected by trained clinicians. This will aid in our assessment of patients’ cardiac function and other safety data.

During follow-up, we will record all the primary and secondary end points and adverse events. All adverse events will be evaluated according to severity, causality, expectedness, and relationship to study treatment. Subjects who develop complications that, in the judgment of principal investigator or sub-investigator, are not suitable to continue the trial will be screened out from the study. Participants will continue with follow-up and may restart study protocol if the clinical situation resolves. Investigators are responsible for the decision to resume the study. If treatment according to the study protocol is clinically insufficient, the study will be suspended and effective treatment should be applied according to the current clinical practice.

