## Discussion

In the EUC-CHF study, we investigate whether early UF (with 24 h after admission) in patients hospitalized for HF worsening and significant fluid overload could help to relieve volume overload and symptom, as well as decrease short-term recurrence of acute HF and rehospitalization.

So far most of the previous researches focused on the benefits of UF in population with LD resistance. A retrospective cohort study from Asian population found UF in patients with decompensated HF and LD resistance achieved lower urine output, greater fluid loss, greater weight loss and a shorter duration of hospitalization than the standard care group. At 90 days, the UF group had fewer emergency department visits and rehospitalizations for HF [17]. In patients with acute decompensated HF due to fluid overload who whether or not have LD resistance, it is unclear about the appropriate time required to start UF. Previous randomized controlled trials (RAPID-CHF, UNLOAD, CUORE and AVOID-HF trials) compared UF to usual care with IV LDs in hospitalized patients with congestion and decompensated HF. Some of the enrolled patients received UF within the first 24 h of admission. The results from these trials all indicated that early UF safely and effectively reduced congestion, decreased length of stay, HF rehospitalizations, and cardiovascular events in acute HF patients. Clinical benefits of early UF in some of these trials last for 3 months to 1 year [4, 8, 18, 19]. Renal function changes were similar between UF and IV LDs in all of these trials. Two studies in acute renal failure after cardiac surgery demonstrated that early recognition of acute renal failure and initiating UF at early-stage are of vital importance. Early UF reduced in-hospital mortality in postcardiac surgery patients with acute renal failure [20, 21]. However, when UF was initiated late during hospitalization, particularly in patients who had already developed acute kidney injury, as in the CARRESS-HF trial, UF may lose its advantage over pharmacologic therapy. This indicated that UF should be considered as an early strategy rather than a rescue treatment. UF stated late when patients developed hemodynamic deterioration may be of less benefit and associated with a higher rate of adverse events such as renal dysfunction [22]. So we will enroll patients with acute decompensated HF due to fluid overload within 24 h after admission.

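### The death endpoints cover only the 30 days after discharge, so deaths during the treated admission are left out of the mortality comparison and silently lower the rehospitalisation count

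*Protocol article*

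**What the plan says.** Study outcomes in the Protocol article gives both outcomes the same starting point, discharge: "HF rehospitalizations for congestive HF in 30 days after discharge, cardiovascular death and all-cause death in 30 days after discharge". The follow-up schedule (text after Fig. 1) sets visits at the end of treatment, then "24 h, 48 h, and 72 h after the end of study treatment, at discharge, and 30 days after discharge".

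Study overview fixes the other end of the stay: "Patient enrollment should be completed and study treatment initiated within 24 h from hospital admission".

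The same follow-up text says that all endpoints and adverse events are recorded. Statistical analysis says that secondary endpoints are summarised as counts and percentages. It gives no denominator for the death or rehospitalisation outcomes.

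Three statements elsewhere bear on the choice of window:
- Background, on ultrafiltration (UF) in patients whose heart failure had not responded to drug treatment: "it was also associated with high incidence of renal function damage and high in-hospital mortality".
- Discussion, on earlier randomised trials: "early UF safely and effectively reduced congestion, decreased length of stay, HF rehospitalizations, and cardiovascular events in acute HF patients".
- Discussion, on what this trial asks, namely whether early UF could "decrease short-term recurrence of acute HF and rehospitalization".

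**The concern.** The trial is meant to assess both efficacy and safety of early UF. UF is given in hospital, and the one mortality signal that the article reports against it arose in hospital. Yet the death endpoints start only when the patient leaves alive.

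Two things follow. First, an imbalance in in-hospital deaths, in either direction, does not show in the mortality comparison. Second, a patient who dies before discharge can never be rehospitalised. An arm with more in-hospital deaths therefore has fewer patients able to contribute a readmission, and its count falls for a reason that is not a benefit. Since preventing readmission within 30 days is part of the trial's stated aim, a reader of the results could be misled on that outcome as well.

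**Working it through.** **Step 1: lay out the windows.** Time for each patient runs as admission, then enrolment and start of treatment (within 24 h), then end of treatment, then discharge, then 30 days. The death endpoints cover only the last segment. I went through the primary and secondary lists in Study outcomes for any item that counts death earlier and found none. The primary items are weight, dyspnoea score and major bleeding. The remaining secondary items are physiological, laboratory, length-of-stay and acute coronary syndrome measures.

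**Step 2: figures in the plan.** The article gives no mortality rate, event rate, effect size or sample-size derivation. The only related arithmetic is 20 + 20 = 40, which is consistent. Everything below except the 20 per arm is an assumption.

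**Step 3: weight of one death.** 1/20 = 5 percentage points of an arm's mortality.

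**Step 4: how likely at least one in-hospital death is.** With an assumed risk p per patient and 40 patients, the chance is 1 − (1 − p)^40.

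| Assumed p | Chance of at least one in 40 |
|---|---|
| 2% | 55% |
| 5% | 87% |
| 10% | 98% |
| 15% | over 99% |

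**Step 5: effect on the mortality comparison.** Assumed deaths are shown as UF / control. The article does not say whether the denominator is all enrolled patients or only those discharged, so both are given.

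| In hospital | After discharge | As written, discharged patients | As written, all 20 | From enrolment, all 20 |
|---|---|---|---|---|
| 3 / 1 | 1 / 1 | 1/17 (5.9%) vs 1/19 (5.3%) | 5% vs 5% | 4/20 (20%) vs 2/20 (10%) |
| 2 / 0 | 1 / 2 | 1/18 (5.6%) vs 2/20 (10.0%) | 5% vs 10% | 3/20 (15%) vs 2/20 (10%) |
| 0 / 2 | 2 / 1 | 2/20 (10.0%) vs 1/18 (5.6%) | 10% vs 5% | 2/20 (10%) vs 3/20 (15%) |

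In the first row a 10-point difference all but disappears. In the second and third rows the direction reverses, once in favour of UF and once against it. The choice of denominator does not rescue the definition.

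**Step 6: effect on the rehospitalisation count.** With 2 in-hospital deaths in one arm and none in the other, 18 and 20 patients can be readmitted. At the same readmission risk r per discharged patient, the expected counts are 18r and 20r. The first is 18/20 = 90% of the second, with no true difference in readmission.

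**Step 7: does the start of the clock matter in itself?** For stays of a and b days, the two 30-day windows share 30 − |a − b| days of time since enrolment. Assumed stays (UF vs control) of 5 vs 7, 6 vs 9 and 7 vs 12 days give 28, 27 and 25 shared days. This is a small effect.

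**Step 8: would moving readmission to day 30 from enrolment be better?** With stays of 5 and 7 days, the days at risk of readmission would be 30 − 5 = 25 and 30 − 7 = 23. The arm discharged earlier would carry more time at risk. The post-discharge window is therefore the better one for readmission.

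**The case against.** The case on the other side has several parts, and most of them limit the point.

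- **Place in the hierarchy.** A reader might infer that the trial's main safety outcome is defective. It is not: the primary safety endpoint is major bleeding. Death is one of many secondary outcomes, summarised descriptively. This stands and lowers the severity.
- **Deaths are not lost.** A reader might infer that in-hospital deaths go unrecorded. Adverse events are recorded and assessed, and visits cover the treatment period and discharge, so these deaths would presumably appear in the safety data. This stands, but recording a death as an adverse event does not put it into the mortality endpoint.
- **Intended meaning.** In a condensed list, the authors may have meant deaths up to the visit 30 days after discharge. That is possible, and no intent to exclude should be read into the text. But the wording states a start at discharge, which is a rule and not a gap left for a fuller document.
- **The background signal.** The in-hospital mortality cited concerned refractory patients. The article also cites a study of UF within 12 h that reported shorter stay and fewer readmissions without change in renal function. So the documents do not show that early UF raises in-hospital deaths, nor that the definition will favour UF. Step 5 shows error in either direction.
- **An arm-dependent clock.** A reader might infer that starting the clock at discharge seriously biases the readmission comparison. Shorter stay with UF is a result of earlier studies and is not yet known here. Readmission can only follow discharge, and Step 7 shows that the shift is small. This objection stands.

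**Conclusion.** The point holds in a limited form. As worded, the cardiovascular and all-cause death endpoints leave out the admission in which UF is given, and in-hospital deaths reduce the rehospitalisation count without this being visible. Each omitted death is worth 5 percentage points in an arm of 20. Omission can hide or reverse a difference, in either direction. At an assumed in-hospital risk of only 2%, at least one such death among 40 patients is more likely than not.

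The reading of the windows rests on the text. The sizes rest on assumed counts and risks, because the article gives none. The primary endpoints and their analysis are not touched. Severity is moderate: worth correcting before the results are tabulated, but no threat to the trial's main conclusions.

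**What to change.** 1. Define all-cause and cardiovascular death as counted from enrolment, in-hospital deaths included, through the existing visit 30 days after discharge. Use all 20 enrolled patients per arm as the denominator.
2. Report the same deaths at day 30 from enrolment as well, since total follow-up in item 1 varies with length of stay and a common fixed time point does not.
3. Keep HF rehospitalisation in the 30 days after discharge. Report beside it, for all enrolled patients, either the combination of death from enrolment or HF rehospitalisation, or rehospitalisation with death as a competing event.

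The cost is a slightly longer endpoint definition and one extra table. No new visit is needed: discharge cannot precede enrolment, so day 30 from enrolment always falls on or before the visit 30 days after discharge.
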